### Recruitment

#### Participants in the internal pilot phase: MACRO Conversation Study

During the internal recruitment pilot phase, potential trial participants will be invited to take part in an embedded qualitative study (MACRO Conversation Study), which is designed to evaluate and optimise trial recruitment. All potential participants will receive a separate participant study information sheet (PIS) for the MACRO Conversation Study whilst waiting in the outpatient department (prior to being seen in the clinic).

#### All participants

Posters and flyers will be placed in outpatient departments with information about the MACRO trial. All potential trial participants will be seen in an outpatient clinic by the PI or Co-I and by the RN or RP, where the aforementioned routine screening assessments will be carried out and the MACRO trial will be verbally introduced by the PI or Co-I and RN or RP. The participant will be informed that in addition to the routine screening assessments, a trial-specific ECG scan (to exclude contraindications to clarithromycin) will be undertaken as well as a pregnancy test (urine test) if the potential participant is of childbearing potential. This information will be included in the main trial consent form.

If interested in the trial, the patient will be provided with a copy of the MACRO PIS to take home and review. The PIS will detail the exact nature of the study, what it will involve for the patient, the implications and constraints of the protocol, the known side effects and any risks involved in taking part. It will be clearly stated that the participant is free to withdraw from the study at any time for any reason without prejudice to future care, and with no obligation to give a reason for their withdrawal. In this event, the choice of treatment will be decided by the patient and their clinical team.

The RN or RP should update the screening log and place a MACRO sticker on the notes, to help identify the patient when they return to the clinic. All patients will be given sufficient time (a minimum of 48 h) to consider the trial and to decide if they would like to take part. Screening logs must be kept up-to-date and completed fully at all times. They are sent to the MACRO trial office for a monthly review.

If the nasal endoscopy and SNOT-22 questionnaire confirm that the patient is a potential MACRO participant but the patient has not received AMT as deemed by the PI or Co-I, the MACRO trial can still be introduced and the participant will be given a copy of the PIS to take home. If, following AMT, symptom control has not been achieved and further treatment is deemed necessary, the patient will be seen in the clinic once more and the MACRO trial discussed in depth.

### Assignment of interventions

#### Sequence generation

Following consent, once trial eligibility has been confirmed, participants will be randomised into the trial by the PI, Co-I, RN or RP. Participants will be randomly allocated to a treatment option using an automated web-based secure randomisation system (RRAMP) provided by the Oxford Clinical Trials Research Unit (OCTRU) with a 1:1:1 allocation ratio. The algorithm will stratify by the presence of polyps and centre using permuted blocks of varying size. The sequence will be generated by the trial statistician.

#### Allocation concealment mechanism and implementation

The centrally managed randomisation will ensure allocation concealment and prevent selection bias. The participant’s identifiable information will be recorded on the randomisation form and will be uploaded to a separate encrypted database at the University of Oxford. Participants allocated to receive the placebo or antibiotic will be assigned a treatment pack number for the corresponding medication. Treatment pack numbers will be randomly generated to ensure allocation concealment and blinding.

#### Blinding (masking)

Blinding of participants and medical staff will be maintained for the comparison of clarithromycin by using a placebo identical in appearance to the antibiotic, although the MACRO trial office can reveal the treatment allocation in case of clinical need. Participants and medical staff will not be blinded to receiving surgery. At the end of each trial participant’s follow-up period of 6 months, the participant will return to normal NHS care. Those who remain symptomatic at this point will receive further treatment as defined by their ENT clinician, which may include being offered steroids, antibiotics or ESS, depending on which arm of the trial they were in. Patients who were allocated to either the placebo or clarithromycin will not be told of their allocation at the end of their 6-month trial period, except in an emergency.

If there is a need to treat a patient in an emergency following a serious adverse reaction (SAR), the treating PI or medical doctor can break the code using the randomisation system to see if the patient was on the active drug. Under these exceptional circumstances, the PI or a member of the site team can unblind the participant using the clinical trial unit’s in-house RRAMP system. If unblinding is required for any other reasons apart from an emergency, site staff must submit a request (through RRAMP) and the request will be reviewed. If appropriate, it will be approved by a member of the central MACRO trial office. Where a SAR is not an emergency to treat but is deemed to be a suspected unexpected serious adverse reaction (SUSAR), then the clinical trial unit will break the code for reporting purposes without necessarily involving the PI. If on breaking the code it is found that the patient was actually taking the placebo, the event will not be classed as a SUSAR.

### Data collection methods

#### Confidentiality

All data will be handled in accordance with the General Data Protection Regulation (EU) 2016/679.

Participants joining MACRO will consent to giving identifiable information that will include their name, email address and telephone contact numbers to allow completion of PROMs and resource-use diaries electronically. If the participant does not consent to completing the documentation electronically, they will be asked instead to provide their home address and telephone number so that the MACRO trial office can send the PROM questionnaires and resource-use diaries by post. This is coordinated centrally by the MACRO trial office. Participants’ identifiable information will be kept securely in a University of Oxford network database, which is separate to the clinical database.

Upon randomisation, the data will be pseudonymised and a study number will be given to each participant. CRFs will not bear the participant’s name, and the study number will be used for identification. Screening logs will list the participant’s initials, year of birth and trial ID to allow identification by site research staff when they return to the clinic.

#### Data collection tools and source document identification

Clinical data will be collected from sites on trial-specific paper CRFs, which will be completed by the local research teams and sent to the MACRO office for data entry. The data will be entered into a validated installation of OpenClinica (www.openclinica.com). The data are held in a secure database and can only be accessed by authorised users via the OpenClinica application, which resides on a webserver hosted and managed by the IT Services Department of Oxford University’s Medical Services Division (http://www.imsu.ox.ac.uk/). Some CRF data may be entered electronically into LimeSurvey. Participants will be requested to complete PROM questionnaires and resource-use diaries electronically using LimeSurvey every week and every 3 months, respectively. A paper version will also be available for participants to complete, which can be returned using prepaid envelopes. Text messaging and email reminders to participants (who have consented to provide their telephone numbers and email addresses) who have not returned the completed PROM questionnaires and resource-use diaries will be used to maximise the completeness of the data. The MACRO trial office may also call participants if there are a number of outstanding PROM questionnaires and resource-use entries not completed by the participant.

If it becomes clear during the pilot phase that there is a low return rate for the prospective online weekly compliance diaries, the trial management group (TMG) will discuss whether to switch to collecting data retrospectively for this aspect of the trial, i.e. at the 6-week, 3-month and 6-month time points.

### Statistical methods

#### Statistical analysis

Full details of the statistical analysis plan will be agreed by the MACRO programme steering committee (PSC) before the data are unblinded. A summary of the planned analyses is presented here. The primary analysis will be according to the randomised allocation, irrespective of subsequent treatment compliance, and conducted at the two-sided 5% significance level with 95% confidence intervals. No adjustment for multiple comparisons is planned, as the comparisons relate to distinct clinical decisions (use or non-use of an antibiotic and surgery versus medical management of one form). Baseline data and participant flow information will be summarised without a formal analysis. The primary outcome will be analysed using linear regression adjusted for baseline SNOT-22 and also for the presence or not of polyps at baseline. Clustering by surgeon will also be accounted for where relevant using an appropriate method (e.g. the cluster robust option in Stata). Secondary outcomes will be analysed similarly using generalised linear models.

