#### Endoscopic sinus surgery

ESS will be performed by consultant rhinologists according to the techniques described by Stammberger, Lund and Kennedy, with surgery proceeding in a stepwise fashion through polypectomy (where present), uncinectomy, middle meatal antrostomy, ethmoidectomy, with additional frontal and sphenoid surgery in selected participants. The extent of surgery to be performed will be decided at an individual participant level but recorded by the operating surgeon as part of the CRF (having first been documented in the medical notes). Instrumentation will not be standardised between centres. Surgery can be undertaken by a registrar under consultant supervision. As this is a pragmatic trial, there will be no specific further standardisation of the ESS procedure at each site.

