### Sample size

The trial will recruit 600 participants. Recruiting participants from 17 centres (therefore, with 17 ESS surgeons) is considered a realistic assumption for the following sample size calculations. The sample size is justified based upon achieving at least 80% statistical power at the two-sided 5% significance level. No adjustment for multiple comparisons has been made, as each of the treatment comparisons are distinct. The minimum clinically important difference has been estimated to be about 8.9 points based upon an anchor study [65]. A 10-point difference in SNOT-22 (0.5 standard deviations (SD), Cohen’s effect size assuming an SD of 20) is often considered a medium-sized effect size and an important difference for this type of outcome. A previous study suggests that a larger effect for surgery against an alternative treatment is plausible, as large as 13.8 [31]. Using target differences of and 8.9 and 10 (and SD of 20) would require and 107 and 90 per group (331 and 270 overall) to achieve 90% statistical power at the two-sided 5% significance level. Offsetting this is the possibility of clustering within the surgical arm, which affects pairwise comparisons involving surgery, and the need to perform a subgroup analysis for CRSwNPs versus CRSsNPs participants. Allowing for clustering (intraclass correlation coefficient of 0.05 and 17 clusters of equal size) in the surgical group would lead to 102 per group (306 overall) for a target difference of 10 points for 90% power. For this trial size and using a target difference of 8.9 but an otherwise identical calculation, there would be 80% power. To enable secondary analyses of treatment interactions by subgroups with or without polyps, the overall sample size was inflated to 600 (after allowing for 10% missing data). This size of study would allow us to detect a difference of 8.9 and 10 (SD of 20) to be detected in all CRS patients with >90% power after adjusting for clustering for the main comparisons involving the ESS group; this is the case even when allowing for the impact of potential variable cluster sizes (cluster size variance of 49). A study of 600 would also likely provide around 50% and 80% power for testing the treatment interaction by subgroup (CRSwNPs versus CRSsNPs) for a target difference of 10 and 13.8, respectively, after allowing for clustering in the surgical arm and an equivalent variation in cluster sizes.

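### Centre stratifies the randomisation but is missing from the stated primary model, so reported standard errors do not match the design: slightly too large for clarithromycin v placebo, dependent on cluster coding for ESS

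*Protocol article*

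**What the plan says.** Under Sequence generation, the article says: "The algorithm will stratify by the presence of polyps and centre using permuted blocks of varying size".

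Under Statistical analysis, the covariates of the primary model are named: "The primary outcome will be analysed using linear regression adjusted for baseline SNOT-22 and also for the presence or not of polyps at baseline". Centre is not among them. The next sentence deals with surgeons: "Clustering by surgeon will also be accounted for where relevant using an appropriate method (e.g. the cluster robust option in Stata". Secondary outcomes are to be handled in a similar way with generalised linear models. The section describes itself as condensed: "A summary of the planned analyses is presented here".

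Under Sample size, surgeon and centre are treated as the same unit: "Recruiting participants from 17 centres (therefore, with 17 ESS surgeons) is considered a realistic assumption for the following sample size calculations". The intraclass correlation of 0.05 is applied there to the surgical group only. No centre ICC for all arms is given anywhere.

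**The concern.** Blocks within centre balance the arms inside each centre, so differences between centres largely cancel from the treatment contrast. A model without centre still counts those differences as residual error, and its SE then describes a less balanced design than the one used.

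Centres may well differ. Intranasal steroids follow local formularies, the extent of surgery is decided patient by patient, and "Instrumentation will not be standardised between centres".

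At stake are the width of the reported confidence intervals and the actual size of the tests. The ESS comparisons carry a second problem. The article does not say to which cluster a medical-arm patient belongs, and the answer changes the SE materially on the same data.

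**Working it through.** **Inputs.** From Sample size: SD 20, so variance 400; target differences 8.9 and 10; two-sided 5%; 17 clusters; surgeon ICC 0.05 in the ESS arm; cluster-size variance 49; 600 randomised with 10% missing, so 540 analysed, or 180 per arm. Assumed, because the article gives no figure: a centre ICC shared by all arms, 0.01 to 0.10.

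**1. The plan's own figure.** Mean cluster size m = 180/17 = 10.59. CV² = 49/10.59² = 0.437. Design effect in the ESS arm = 1 + ((1 + 0.437) × 10.59 − 1) × 0.05 = 1.71. SE = 20 × √((1 + 1.71)/180) = 2.45. Power is 95.1% at 8.9 points and 98.2% at 10, so the stated power above 90% reproduces.

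**2. Clarithromycin v placebo, analytic.** With centre omitted, the reported SE is √(2 × 400/180) = 2.108. The true SE under centre-stratified blocks is √(2 × 400 × (1 − ρ)/180), which is 2.055 at ρ = 0.05. The ratio is 1/√(1 − ρ), and the actual type I error is 2 × (1 − Φ(1.96 × ratio)).

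| Assumed centre ICC ρ | Reported / true SE | Actual type I error |
|---|---|---|
| 0.01 | 1.005 | 4.9% |
| 0.05 | 1.026 | 4.4% |
| 0.10 | 1.054 | 3.9% |

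Power at 8.9 points with ρ = 0.05 is 99.0% with centre omitted and 99.1% with centre included.

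**3. The same comparison, simulated** (17 unequal centres, blocks within centre and polyps, 2,000 runs, ρ = 0.05). With centre omitted, the mean reported SE is 2.104 against an empirical SE of 2.039, with 4.1% rejections. With centre fixed effects, the reported SE is 2.060 with 4.8% rejections. The Monte Carlo error of a rejection rate near 5% is √(0.05 × 0.95/2000) = 0.5 percentage points, so the analytic table is the firmer guide. The empirical SE is 2.039 with or without centre: the estimate itself gains or loses nothing.

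**4. ESS v a medical arm, centre omitted, simulated.** ESS-only clustering means cluster-robust SEs by surgeon, with each medical patient as a separate cluster.

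| Centre ICC | Surgeon ICC | Coding | Mean SE v true | Ratio |
|---|---|---|---|---|
| 0.05 | 0 | ESS arm only | 2.34–2.35 v 2.03–2.10 | 1.11–1.16 |
| 0.05 | 0.05 | ESS arm only | 2.605 v 2.389 | 1.09 |
| 0.05 | 0 | all patients | 1.99–2.00 v 2.07–2.10 | 0.95–0.96 |
| 0.05 | 0.05 | all patients | 2.319 v 2.389 | 0.97 |
| 0 | 0.05 | ESS arm only | 2.35 v 2.44 | 0.96 |

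Ranges come from repeated simulations of the same scenario. Depending on how the surgeon variance is added, the second row lies at about 7% to 9%. The excess under ESS-only coding moves with the assumed centre ICC. With no surgeon variance it is about 3% at 0.01 (2.12 v 2.06), 4% at 0.02 (2.18 v 2.09) and 29% at 0.10 (2.619 v 2.031).

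**5. Can centre stand in for the surgeon term?** No. With centre and surgeon ICC both 0.05, centre fixed effects with model-based SEs report 2.074 against an empirical 2.389, and type I error is 8.3%. At a centre ICC of 0.10 it is 8.5%.

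**6. Centre and surgeon together.** Centre fixed effects with SEs clustered by centre, at centre ICC 0.10 and surgeon ICC 0.05, give 2.340 against 2.304 with 4.5% rejections.

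**The case against.** The article calls its analysis section a summary, and the statistical analysis plan is not shown. Whether centre is fixed or random, and how clusters are coded, are details commonly left to that plan. This stands for the coding. It does not dispose of the omission, because the summary names its covariates and takes one of the two stratifiers.

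The surgeon sentence may already cover the ESS comparisons. With one surgeon per centre, clustering all patients by surgeon or centre brings the SE close to the design. This also stands, as one permitted reading. The sample size section places clustering in the surgical group, so ESS-only coding is permitted too. Neither reading reaches clarithromycin v placebo.

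A reader might infer more than the article supports:

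- *That precision or power is lost.* Under stratified blocks the estimator's variability is the same with or without centre; only the reported SE changes.
- *That the ESS analysis as written has an SE 16% too wide and about 2.7% type I error.* This needs ESS-only coding, no surgeon variance, and the plan's 0.05 moved from the ESS arm to a centre effect in all arms. Under the plan's own assumption of surgeon variance alone, ESS-only coding gives a slightly small SE (2.35 v 2.44, 6.4% rejections).
- *That adding centre narrows the ESS interval by 13%.* That figure comes from model-based SEs with no surgeon variance. Where surgeon variance exists, that analysis is anticonservative.
- *That the polyp interaction suffers most.* No calculation supports this, and the article calls that analysis exploratory.

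**Conclusion.** The point holds in limited form. A stratification factor is left out of a stated covariate list without a reason, and the reported SEs then do not match the design.

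For clarithromycin v placebo the direction is known and the size small: the SE is 0.5% to 5% too large over an assumed centre ICC of 0.01 to 0.10, the test is slightly conservative, and power is practically unchanged.

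For ESS comparisons the size and even the direction depend on coding and on variance components that the article does not settle. At a centre ICC of 0.05 the result runs from about 7% to 16% too wide (ESS arm only) to close to or slightly below the true value (all patients). Even with a centre ICC of 0.10 and a surgeon ICC of 0.05, ESS-only coding keeps simulated power at 91.3% for 8.9 points, so the main comparisons are not endangered. The reason to act is that the ambiguity is avoidable and should be closed before unblinding.

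**What to change.** In the primary model, list the adjustment terms as baseline SNOT-22, presence of polyps, and centre (in all arms). Use the same terms for secondary outcomes.

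For every comparison involving ESS, keep an explicit surgeon term for the ESS arm in addition to centre, and state which cluster medical-arm patients belong to. Centre fixed effects with SEs clustered by centre behaved acceptably in step 6. A random surgeon effect confined to ESS patients is another option, but it was not simulated here. Do not drop the surgeon term once centre is in the model.

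If centre is left out on purpose, say why.

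The cost is one line of wording in the analysis plan. No new data are needed, because the randomisation system already holds each participant's centre.

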#### Sensitivity and other planned analyses

The impact of missing primary outcome data will be assessed in sensitivity analyses, e.g. the multiple imputation approach, as appropriate. Exploratory subgroup analyses will assess the impact of the presence of polyps under the treatment effect. The impact of compliance will be evaluated using a complier average causal effect approach or a similar approach.

#### Interim analysis

No interim analyses are anticipated prior to completion of the follow-up for the designated time points. This is due to the nature of the trial, the primary outcome and the desire for reasonable precision to assess the subgroups for CRSwNPs and CRSsNPs.

### Data monitoring

Details of the committee personnel can be found in Additional file 1: Appendix 1.

#### Trial management group

The TMG will include the chief investigator, lead collaborative investigator, trial staff and members of the MACRO programme. A member of the sponsor team will also be invited to attend. The TMG will be responsible for overseeing the trial. Monthly TMG teleconferences will take place at the start of the trial, and at least two face-to-face meetings will take place annually.

The TMG will review recruitment figures, SAEs and substantial amendments to the protocol prior to submission to the research ethics committee or the Medicines and Healthcare Products Regulatory Agency (MHRA). All PIs will be kept informed of substantial amendments through their nominated responsible individuals. There will be a TMG charter for the MACRO trial.

#### Trial steering committee

As MACRO forms part of a programme of work, there will be an overarching independent PSC for the duration of the programme. The PSC contains members experienced in each specialist area of the MACRO programme. Membership also includes an experienced triallist, a clinician, a statistician, a qualitative researcher, a health economist, a GP and a patient. During the MACRO trial, the PSC will assume the role of the trial steering committee (TSC) and will provide overall supervision of the trial. The TSC will review the recommendations of the independent data safety and monitoring committee (DSMC) and, on consideration of this information, recommend any appropriate amendments or actions for the trial as necessary. The TSC acts on behalf of the funders and sponsor.

#### Data safety monitoring committee

The role of the DSMC is to provide independent advice on data and the safety aspects of the trial. The committee will meet annually to review safety data and any other issues. There will be a DSMC charter for the MACRO trial.

